## Abstract

**Background:**

The behavior of arterial blood pressure in postpartum of women with hypertension and pregnancy and the best treatment for very high blood pressure in this period still need evidence. The Cochrane systematic review assessing prevention and treatment of postpartum hypertension found only two trials (120 patients) comparing hydralazine with nifedipine and labetalol for the treatment of severe hypertension and did not find enough evidence to know how best to treat women with hypertension after birth. Although studies have demonstrated the effectiveness of treatment with captopril, side effects were reported. Because of these findings, new classes of antihypertensive drugs began to be administered as an alternative therapy. Data on the role of clonidine in this particular group of patients, its effects in the short and long term are still scarce in the literature.

**Objectives:**

To determine the effectiveness of clonidine, compared to captopril, for the treatment of postpartum very high blood pressure in women with hypertension in pregnancy.

**Methods/design:**

The study is a triple blind randomized controlled trial including postpartum women with diagnosis of hypertension in pregnancy presenting very high blood pressure, and exclusion criteria will be presence of heart disease, smoking, use of illicit drugs, any contraindication to the use of captopril or clonidine and inability to receive oral medications.

Eligible patients will be invited to participate and those who agree will be included in the study and receive captopril or clonidine according to a random list of numbers. The subjects will receive the study medication every 20 minutes until blood pressure is over 170 mmHg of systolic blood pressure and 110 mmHg diastolic blood pressure. A maximum of six pills a day for very high blood pressure will be administered. In case of persistent high blood pressure levels, other antihypertensive agents will be used.

During the study the women will be subject to strict control of blood pressure and urine output. This proposal has already obtained approval of the local Institutional Review Board of the coordinating center (IMIP, Recife, Brazil) and of the National Council for Ethics in Research (CONEP) of the Brazilian Ministry of Health.

**Trial registration:**

Clinical Trials Register under the number NCT01761916.

## Introduction

Hypertension complicates approximately 10% of pregnancies [1] and is the leading cause of maternal death in Brazil [2] and the third leading cause in the world [3]. It also entails increased maternal morbidity associated with complications such as eclampsia, HELLP syndrome, hemorrhage, pulmonary edema, renal failure and coma [4]. Perinatal morbidity and mortality are also increased [5]. Much has been studied about the repercussions of hypertension for the mother and the fetus, but there are relatively few studies evaluating the behavior of postpartum blood pressure, its impact and what is the better pharmacological treatment during this period [6-11].

Although the true prevalence of postpartum hypertension is unknown, it is important to monitor blood pressure levels after delivery, because they can continue to increase in women with previous diagnosis of hypertension or hypertensive crisis can develop only postpartum [6]. According to a recent review of the etiology and management of postpartum hypertension-preeclampsia the reported prevalence of new onset postpartum hypertension or preeclampsia ranges from 0.3–27.5% [6]. Complications of severe hypertension include stroke, eclampsia, congestive heart failure, acute pulmonary edema, renal failure and death [4,12]. One study demonstrated that 44% of eclampsia occurs in the postpartum period, usually in the first 48 hours [13].

It has been shown that blood pressure increases progressively over the first five days after birth, peaking on three to six days after delivery [14] It is believed that this pattern of blood pressure results from the mobilization from the extravascular to intravascular space of six to eight liters of total body water and the and the 950 mEq of total body sodium accumulated during pregnancy. The urinary sodium excretion was observed on days 3–5 postpartum [15], and it was postulated to result from an increase in atrial natriuretic peptide (ANP). ANP have roles in natriuresis, inhibition of aldosterone and angiotensin II and vasopressin [16] and was found to rise during the first week after delivery [17].

Hypertension, proteinuria and biochemical changes caused by pre-eclampsia may persist for six to 12 weeks postpartum [18]. Although it has been postulated that the exposure time could be short to cause target organ damage, the presence of kidney disorders and persistence of hypertension in subsequent evaluations have been demonstrated, which generated doubts about the best management in this period [19].

The effectiveness of different antihypertensive medications in the postpartum period has not been adequately assessed. In the Cochrane systematic review specifically evaluating prevention and treatment of postpartum hypertension, nine trials were included, four of those evaluating prevention furosemide, nifedipine and L-arginine compared to placebo, three studies evaluated timolol, oral hydralazine, or oral nifedipine compared with methyldopa and only two studies (120 patients) evaluated the treatment of severe hypertension with intravenous hydralazine, labetalol intravenous or sublingual nifedipine. In these last studies, there were no maternal deaths or hypotension. Use of additional antihypertensive therapy did not differ between groups (RR 0.58, 95% CI 0.04 to 9.07; two trials), but the trials were not consistent in their effects. The reviewers conclude that there are no reliable data to guide management of women who are hypertensive postpartum. Any antihypertensive agent used should be based on a clinician's familiarity with the drug [9]. In the setting of postpartum hypertensive crisis there is no consensus, although recently experts have recommended intravenous labetalol or hydralazine if there is persistent elevations in blood pressure (BP) to levels ≥160 mmHg systolic and/or ≥ 110 mmHg diastolic [6].

Captopril is an inhibitor of angiotensin I converting enzyme and is used for treating hypertensive crisis [20]. Although the use of captopril during pregnancy is contraindicated [21], its use after delivery has been described [22] and the drug is compatible with lactation [23,24]. However, side effects have been reported such as dry cough, hypotension and decreased renal function [24].

The use of captopril postpartum was tested in an open clinical trial with 79 patients with a diagnosis of pre-eclampsia and eclampsia. Of these, 71 received captopril at a dose of 25 mg at intervals of 30 minutes up to three doses and the remaining eight received hydralazine intravenously at a dose of 5 mg, maximum of four doses with an interval of 20 minutes. Of the mothers who received captopril, 52 (73.3%) responded satisfactorily to the drug with a reduction of up to 25% of blood pressure levels. Regarding the number of doses administered, 20 patients (38%) required one dose, 26 (50%) two doses and six (11%), three doses. No adverse maternal effects were observed. There were also no changes in diuresis and creatinine levels in the neonate. Given these findings, the authors recommend the use of captopril for the management of hypertensive crisis in the puerperium [22]. Low levels of captopril are found in breast milk with small amounts of the drug ingested by the infant. So, it would not be expected any adverse effects in breastfed infants [23-25]. Notwithstanding, no randomized controlled trials (RCT) were found comparing captopril with other drugs or placebo in postpartum hypertensive women.

Clonidine belongs to the class of alpha-2-agonist with central action [26] and began to be used in postpartum women with some restriction on the use of ACE inhibitors and its hypotensive effect for peak pressure was satisfactory [27]. The drug is compatible with lactation and no typical clonidine side effects were seen in infants whose mothers were taking clonidine [28,29]. What is not known yet is how long clonidine lowers blood pressure and what is the duration of its effect compared to captopril.

There were no reports in the database searched (Embase, Scopus, Cochrane Library, Lilacs and Pubmed), neither randomized controlled trials that prove the effectiveness of clonidine for the treatment of hypertensive crisis in this particular group of patients or studies comparing this drug with captopril.

The objective of this study is to determine the effectiveness of clonidine compared to captopril for treatment of very high blood pressure in postpartum women in a randomized controlled trial.

### Objectives and hypothesis

The overall objective is to determine the effectiveness of clonidine compared to captopril, for treatment of postpartum women with very high blood pressure.

#### Specific objectives

Analyzing postpartum patients with very high blood pressure randomized to receive clonidine or captopril, the specific objectives are to compare:

#### Primary outcome

• Mean arterial blood pressure

#### Secondary outcomes

• Need of another antihypertensive agent for very high blood pressure;

• Need to maintain the antihypertensive therapy;

• Daily mean systolic blood pressure

• Daily mean diastolic blood pressure

• Number of days with hypertensive peaks

• Daily mean of hypertensive peaks

• Number of days until blood pressure control

• Number of days using antihypertensive drugs for treatment of hypertensive peaks

• Number of antihypertensive drugs associated

• Need for sodium nitroprusside to control hypertension

• Number of days of obstetric ICU stay.

### Main hypothesis

In postpartum patients with postpartum very high blood pressure randomized to receive clonidine compared to the women receiving captopril:

• Mean blood pressure is lower

• Need of other antihypertensive agents for very high blood pressure is lower

• Need to maintain other antihypertensive agents is lower

• Daily mean systolic blood pressure is lower

• Daily mean diastolic blood pressure is lower

• Number of days with hypertensive peaks is lower

• Number of days until blood pressure control is lower

• Number of days using antihypertensive drugs for treatment of hypertensive peaks is lower

• Need of association with other antihypertensive drug for treatment of hypertensive peaks is lower

• Number of antihypertensive drugs associated is lower

• Need for sodium nitroprusside to control hypertension is lower

• Number of days of obstetric ICU stay is lower.

## Methods/design

### Study design

The present study is a triple blind randomized controlled trial. The SPIRIT guidelines were used to prepare this protocol [30].

### Study population and location

The study population will include all eligible women with hypertension in pregnancy admitted to the obstetrical ICU in the postpartum period.

### Eligibility criteria

The inclusion criterion is the presence of very high blood pressure in postpartum women with hypertension in pregnancy receiving magnesium sulfate for prevention or treatment of eclampsia (which includes both severe and superimposed preeclampsia or eclampsia cases). Exclusion criteria are: other associated maternal diseases (such as diabetes mellitus, collagen vascular disease, glomerulonephritis, lung and heart disease); smoking; use of any antihypertensive agent for very high blood pressure before admission to ICU or illicit drugs that may interfere with maternal hemodynamics; contraindications to the use of captopril (acute kidney injury, chronic liver disease and hypersensitivity to the drug) and contraindications to the use of clonidine (sick sinus syndrome, chronic liver disease and hypersensitivity to the drug).

### Procedures for selecting participants and randomization

Eligible patients will be invited to participate and those who agree will be included in the study and receive clonidine or captopril according to a random list of numbers generated by the Random Allocation Software (Ispharan Iran), version 1.0. This list of randomization will be provided by the statistician to the pharmacist who will be responsible for preparing the packages containing either the clonidine or captopril, both in an identical presentation, with the identification number of list labeled. This procedure will be followed in order to guarantee the concealment of allocation of patients in both arms. Considering both drugs have rare identifiable immediate effects, either patients and medical staff should be blind of the intervention condition in each case. Study medication, after delivered by the pharmaceutical industry to the pharmacy of the coordinating center, will be packed as previously described and according the random list. The drugs will be kept at the ICU under the responsibility of the nurse, and when included the patient will receive the drug in the package corresponding to the inclusion. The subjects will receive the study medication at the moment of the inclusion (very high blood pressure) and the drug will be repeated after 20 minutes if the blood pressure levels have not responded to the administered drug, to a maximum of six doses. Other episodes of very high blood pressure during the day will be managed likewise, respecting the maximum of six doses of the study medication a day.

If attending physicians observe that the blood pressure levels do not improve or if the 6 doses of medication for very high blood pressure where used, another drug for very high blood pressures (hydralazine or sodium nitroprusside) will be used, according to the physicians’ choice and judgment. During the study period other anti hypertensive agents used for maintenance may be initiated according to the physicians’ choice and judgment.

During the observation period the women will be subject to the ICU routine which includes strict control of blood pressure and urine output (diuresis evaluated spontaneous or urinary catheter). Laboratory tests will be performed at regular intervals of 24 hours (blood count, coagulation, renal and hepatic function).

### Sample size calculation

To calculate the sample size, as there were no studies evaluating the use of clonidine for the treatment of hypertensive crisis in the puerperium, nor a comparison with captopril for this purpose, we conducted a pilot study with 30 postpartum women with hypertensive disorders, 15 of each group (captopril vs. clonidine) in order to obtain the most suitable calculation of the sample.

After completion of the pilot study and through statistical calculator Open Epi 3.01 (CDC, GA), the daily mean of hypertensive peaks in each group (called A and B for this purpose) was used to calculate the sample with a power of 90% and a confidence level of 95%. Considering a mean of 2.8 hypertensive peaks/day in group A, with a standard deviation of 2.0 and a mean of 6.2 hypertensive peaks/day with a standard deviation of 6.2 in group B, a total of 90 patients was estimated already predicting eventual losses or differences between the groups (original sample size of 78 women).

### Daily mean of hypertensive peaks

#### Variables

##### Independent variable

• Use of clonidine or captopril

#### Dependent variables

Mean arterial blood pressure, need of another antihypertensive agent for very high blood pressure, need to maintain the antihypertensive therapy, daily mean systolic blood pressure, daily mean diastolic blood pressure, number of days with hypertensive peaks, number of days until blood pressure control (absence of episodes of very high blood pressure), number of days using antihypertensive drugs for treatment of hypertensive peaks, need of association with other antihypertensive drugs for treatment of hypertensive peaks, number of antihypertensive drugs associated, need for sodium nitroprusside to control hypertension and number of days of obstetric ICU stay.

### Main outcomes

• Hypertensive disorders of pregnancy: defined according to the National High Blood Pressure Education Program Working Group on High Blood Pressure in Pregnancy [18].

• Very high blood pressure episode: systolic blood pressure (SBP) ≥ 180 mmHg and/or diastolic blood pressure (DBP) ≥ 110 mmHg [18].

• Control of arterial blood pressure: absence of episodes of very high blood pressure.

#### Data collection procedures

##### Data collection

The data will be entered in a specific database created in the public domain statistical program Epi-Info version 7 for Windows vista. The data entry will be made after reviewing the forms. Every month this database will be reviewed by the researcher, obtaining listing of variables and correcting any inconsistencies or missing information from the query to the forms. Data missing in medical charts should be collected from other sources, such as hospital's database, prenatal cards, transference documents and others. Tests of consistency and frequency distribution tables of the main variables will be obtained to correct any errors. In the case of finding inconsistencies or lack of information, the forms will be consulted. At the end of typing, listings for the final correction will again be obtained with creation of the definitive database, which will be submitted to the tests of cleaning and consistency of information and hence statistical analysis will be performed.

### Data analysis plan

The data analysis will be performed using the public domain software Epi Info version 7 (Centers for Disease Control and Prevention, Atlanta, GA), or the newest available version under the intention to treat principle. The statistician and the investigators will remain blind to the treatment groups until the tables will be prepared and the analysis concluded. The approach for analysis will be that showed in Figure 1 using an intention-to-treat strategy and following the correspondent recommendations from the CONSORT statement [31]. The characteristics of the participants in each group will be compared with Student’s *t* test for continuous variables with normal distribution and Mann–Whitney U test for discrete and ordinal variables or those with non-normal distribution. Repeated measures analysis of variance (ANOVA) will be used for comparing daily mean blood pressure in both groups. Categorical variables will be compared with Pearson’s χ [2] test or Fisher’s exact test, as appropriate. P values for all tests will be two tailed at a 5% level of significance. Risk ratios and their 95% confidence intervals will be calculated as a measure of relative risk. The number needed to treat (NNT) and its 95% confidence interval will be calculated for the outcomes in which a beneficial effect of dexamethasone treatment is achieved, using the EBM calculator [http://moosenose.com/EBCalculator.htm]; in case of adverse effects the number needed to harm (NNH) and its 95% confidence will also be calculated.

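### Repeated measures ANOVA of daily mean blood pressure does not suit follow-up of unequal length: run on complete cases it would exclude women with short stays, and it could bias the comparison

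*Protocol article*

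**What the plan says.** The Data analysis plan gives one method for blood pressure over time: "Repeated measures analysis of variance (ANOVA) will be used for comparing daily mean blood pressure in both groups". The same section says the analysis is done "using an intention-to-treat strategy and following the correspondent recommendations from the CONSORT statement", and that "P values for all tests will be two tailed at a 5% level of significance". It does not say how many days enter the ANOVA, or what happens to a woman who lacks some of them.

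The primary outcome is given only as "Mean arterial blood pressure", with no time window. Daily mean systolic and diastolic pressure are secondary outcomes.

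On follow-up, Study population and location recruits women admitted to the obstetric ICU. Procedures for selecting participants and randomization adds: "During the observation period the women will be subject to the ICU routine which includes strict control of blood pressure". The length of that period is not fixed. Secondary outcomes include "Number of days of obstetric ICU stay" and days until blood pressure control. Under Main hypothesis both are expected to be lower on clonidine; for ICU stay the wording is "Number of days of obstetric ICU stay is lower".

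**The concern.** Classical repeated measures ANOVA works on a complete rectangle: every woman must have a value on every analysed day. This protocol expects stays of different lengths, possibly different by arm, and sets no common window. Forcing such data into the rectangle excludes the women with short stays.

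Stay is a consequence of randomized treatment if the protocol's own hypothesis is right. Selecting on it breaks the randomized comparison that intention to treat is meant to protect. At the least, women and power are lost. If the women who leave early are those with lower pressures, the remaining groups are no longer comparable and the estimated drug difference can be wrong. The outcomes exposed are the daily mean pressures and, if it is analysed by the same method, the primary outcome.

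**Working it through.** **1. The plan's own figure.** The protocol gives no blood pressure mean, SD or target difference. Its sample size rests on hypertensive peaks per day (Sample size calculation: 2.8, SD 2.0, against 6.2, SD 6.2; 90% power, 95% confidence). Assuming equal allocation:

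n per arm = (2.0² + 6.2²)(1.960 + 1.282)² / (6.2 - 2.8)² = 42.44 × 10.51 / 11.56 = 38.6, so 39 per arm and 78 in total, as stated.

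The rise to 90 allows for (90 - 78)/90 = 13.3% losses. Two things carry over: the size of that allowance, and the very unequal pilot SDs.

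**2. Assumed inputs for blood pressure (none is from the documents).** Control-arm mean arterial pressure is 115 mmHg on day 1, falling 2 mmHg per day. Between-woman SD is 8 and within-woman SD is 6. The true difference (control minus active) is 5 mmHg. Under the hard exit rule a woman leaves after a daily mean below 108. Under the soft rule the chance of leaving rises as pressure falls. The complete-case estimate is the arm difference in the K-day mean among women with all K days.

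**3. Two days, hard rule, by hand.** The day-1 SD is √(64 + 36) = 10 and the day-to-day correlation is 64/100 = 0.64. Keeping only women at or above 108 on day 1 raises the two-day mean by 10 × (1 + 0.64)/2 × λ = 8.2λ, where λ = φ(a)/[1 - Φ(a)] and a = (108 - arm mean)/10.

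- Control: a = -0.7; kept 75.8%; λ = 0.3123/0.7580 = 0.412; rise 3.38.
- Active: a = -0.2; kept 57.9%; λ = 0.3910/0.5793 = 0.675; rise 5.54.

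Estimate = 5 - (5.54 - 3.38) = 2.84 mmHg.

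**4. Simulation, equal spread, true difference 5 mmHg (400,000 women per scenario).**

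| Days analysed | Hard rule: estimate (kept, control / active) | Soft rule: estimate (kept, control / active) |
|---|---|---|
| 2 | 2.8 (76% / 58%) | 3.7 (70% / 56%) |
| 3 | 2.3 (61% / 40%) | 3.1 (50% / 34%) |
| 4 | 2.0 (49% / 28%) | 2.7 (36% / 21%) |

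The two-day hard-rule result agrees with the hand calculation. Exclusions of 24 to 64% in one arm and 42 to 79% in the other compare with an allowance of 13.3%.

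**5. Unequal between-woman SD (three days, hard rule).**

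| SD control / active | Estimate, true 0 | Estimate, true 5 |
|---|---|---|
| 5 / 12 | -5.1 | -3.1 |
| 8 / 12 | -3.1 | -1.0 |
| 12 / 8 | 3.1 | 5.3 |
| 12 / 5 | 5.1 | 7.7 |

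Selection on low pressure raises the mean more in the arm with the wider spread. The bias can therefore dilute, reverse or exaggerate a difference, or create one where none exists.

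**6. When there is no bias.** With exit unrelated to pressure, even in one arm only, the estimate stayed at 5.0; only women and power were lost. With no true difference and equal spread it stayed at 0.

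**The case against.** The strongest reply is that the harmful chain is not in the text. A reader might infer that women leave the ICU once their pressure is controlled, so that the ANOVA discards the early responders and pulls the result toward no difference. The documents do not support that as fact:

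- **Exit rule.** No section gives a discharge rule, ties discharge to control, or says measurement stops at ICU exit. The Discussion says only that better treatment may shorten hospital stay. Control is defined under Main outcomes as absence of very high pressure episodes, not as a daily mean below a threshold.
- **Exclusion.** Complete-case analysis is not stated. A window short enough to cover every woman, continued measurement after the ICU, or a mixed-model form of repeated measures analysis would avoid it, and such detail may sit in a fuller document. Data collection provides for retrieving missing chart data, but that cannot supply readings never taken.
- **Direction.** Dilution is the equal-spread result. The only spread figures in the protocol, 2.0 and 6.2 for peaks per day, are far from equal.
- **Power.** One assumed scenario (45 per arm, four days, true effect 6 mmHg, exit below a daily mean of 106) gives 20% power for complete-case ANOVA and 87% for a mixed model. Exit decided by the last recorded value is exactly the case that suits the mixed model. Varying the starting mean, daily fall and threshold moved complete-case power from 15% to 73%. No such figure is a property of this trial.
- **Primary outcome.** The ANOVA sentence does not name it, so that link is an inference. Omitting the inclusion pressure as a covariate is an efficiency choice, not an error.

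All of this stands and limits the claim. It does not remove the mismatch between a named method that needs equal follow-up and a design that expects unequal follow-up. That is a fault in what the article states, not a detail left to an analysis plan.

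**Conclusion.** The point holds in conditional form. The named method fits poorly with a varying number of daily values per woman. If it is run on complete cases, women with short stays are excluded, intention to treat is not honoured and power is lost. Bias needs one further condition, exit that depends on pressure, which is plausible but unstated. Its direction is toward no difference only when spread is similar in both arms.

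The size is illustrative: a true 5 mmHg becomes about 2.0 to 3.7 mmHg with equal spread, and anything from -3.1 to 7.7 mmHg with unequal spread. All blood pressure inputs are assumed. This is a cheap and worthwhile improvement to the plan, not proof that the planned result would be wrong.

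**What to change.** Replace the ANOVA sentence with wording such as: *Daily mean blood pressure will be analysed with a likelihood-based linear mixed model using all available days from all randomized women, with treatment, day, treatment-by-day and the inclusion blood pressure as covariate. The treatment difference averaged over a fixed initial number of days will be reported with its 95% CI.* The number of days should be set before unblinding. The inclusion pressure is available for every woman, because a very high reading triggers entry.

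The cost is plan wording and, if Epi Info does not fit such models, other free software. Treatment and data collection are unchanged. The downside is that the model assumes missing later days are explained by the recorded earlier pressures. If women leave for reasons related to pressure that those values do not capture, some bias remains.

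### The named blood-pressure model has no baseline covariate although every woman has a pre-dose reading; the comparison stays valid but gives up precision that costs nothing to recover.

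*Protocol article*

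**What the plan says.** All references are to the Protocol article.

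- **Primary outcome** gives only "Mean arterial blood pressure", with no time point or summary. **Secondary outcomes** lists daily mean systolic and daily mean diastolic pressure.
- **Data analysis plan** names one method for blood pressure, a repeated-measures ANOVA that "will be used for comparing daily mean blood pressure in both groups". It mentions no covariate, change score or adjusted analysis.
- The same section says "The characteristics of the participants in each group will be compared with" a t test or a Mann–Whitney test, depending on the variable. Categorical variables get a chi-square or Fisher test.
- **Eligibility criteria** makes very high blood pressure the condition for entry. **Procedures for selecting participants and randomization** times the first dose: "The subjects will receive the study medication at the moment of the inclusion (very high blood pressure". **Main outcomes** defines an episode as "systolic blood pressure (SBP) ≥ 180 mmHg and/or diastolic blood pressure (DBP) ≥ 110 mmHg".
- Allocation is "according to a random list of numbers generated by the Random Allocation Software". No stratification on blood pressure is described.

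**The concern.** The pre-dose pressure is probably the most obvious predictor of later pressure, and the entry rule implies that it exists for every woman. The only model named for pressure does not use it, and the randomisation as described does not balance it. With about 45 women per arm, the arms can differ by chance at the start, and an unadjusted comparison carries part of that difference into the treatment estimate.

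What is at stake is efficiency: a wider confidence interval and lower power for the blood-pressure outcomes than the same data could give. There is also a smaller point about prespecification. If no covariate is fixed in advance, a decision to adjust could later be made after the baseline table has been seen, which would be data-driven.

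**Working it through.** **The plan's own figure.** Sample size calculation gives means of 2.8 and 6.2 peaks/day, SDs of 2.0 and 6.2, 90% power and 95% confidence.

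- n per arm = (SD₁² + SD₂²)(z₀.₉₇₅ + z₀.₉₀)² / (difference)² = (4 + 38.44)(10.507) / 3.4² = 38.58, rounded up to 39, so 78 in total.

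This reproduces the stated 78, which the plan raises to 90 (45 per arm if allocation is 1:1, an assumption). The calculation concerns peaks/day, so nothing below changes it.

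**What adjustment is worth.** Let r be the correlation between the pre-dose reading and the outcome. The documents do not give it, so every value here is assumed. For one post-dose value, adjustment multiplies the outcome variance by 1 − r². With 45 per arm, this is worth 45/(1 − r²) unadjusted women per arm.

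| r | 1 − r² | variance reduction | equivalent n per arm |
|---|---|---|---|
| 0.14 | 0.98 | 2% | 45.9 |
| 0.25 | 0.94 | 6% | 48.0 |
| 0.3 | 0.91 | 9% | 49.5 |
| 0.5 | 0.75 | 25% | 60.0 |

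**Why the range starts so low.** Admitting only women above a threshold narrows the spread of the baseline and so lowers r. If the baseline is normal and cut at +1 SD (assumption), its SD shrinks to u = 0.446 of the unrestricted value, and

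- restricted r = r·u / √(1 − r² + r²u²).

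Unrestricted correlations of 0.3, 0.5 and 0.7 become 0.14, 0.25 and 0.40. The gains fall to 2%, 6% and 16%.

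**Two facts that push the other way.**

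- Entry is on systolic and/or diastolic pressure with no ceiling, so mean arterial pressure is not cut at one point. Taking it as diastolic plus one third of the pulse pressure, 185/90 gives 90 + 95/3 ≈ 122 mmHg and 210/130 gives 130 + 80/3 ≈ 157 mmHg. Both qualify.
- Averaging over days raises the gain. For the mean of k daily values with a common correlation r throughout (assumption), the factor is 1 − r² / [(1 + (k − 1)r)/k]. With k = 3 and r = 0.3 it is 1 − 0.09/0.533 = 0.83. With r = 0.5 it is 1 − 0.25/0.667 = 0.63. These two values make no allowance for range restriction.

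**Chance imbalance.** With 45 per arm, the baseline difference has a standard error of √(2/45) = 0.211 SD, so its 95% range is ±1.96 × 0.211 = ±0.41 baseline SD. About r times that carries into an unadjusted estimate: 0.14 × 0.413 = 0.06 outcome SD, up to 0.5 × 0.413 = 0.21 outcome SD. This is the precision loss seen in a single trial, not a second harm to be added to it.

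**The case against.** The strongest reply is that the point is drawn from silence. The article does not say that the analysis is unadjusted. It does not rule out a covariate, or the inclusion reading as one of the repeated time points, and a condensed article may leave such detail to a fuller plan. This stands as a limit on wording: the accurate statement is that no covariate is named. It does not remove the point, because the section does name a specific model, and adding a measurement already taken would improve that model.

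Four stronger readings are tempting, and the documents support none of them:

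- **That the analysis is invalid or biased.** Allocation is random, so the unadjusted comparison is unbiased and its type I error is valid. Its standard error already allows for chance imbalance.
- **That the primary estimate is certainly affected.** The ANOVA sentence refers to daily mean pressure, and the outcomes labelled as daily means of pressure are secondary. The primary outcome has no stated summary. Applying the same model to it is the natural reading, but it is an inference.
- **That the loss is likely to be material.** No SD or correlation is given, and the entry threshold that guarantees a reading also weakens its predictive value. The loss can be material; the documents cannot show that it will be.
- **That testing participants' characteristics damages the result.** The sentence does not use the word baseline, although that is its natural meaning. Such p values are uninformative under randomisation, but they change no treatment estimate. Nor does the text say that they replace adjustment.

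**Conclusion.** The point holds as one of efficiency. The plan names repeated-measures ANOVA for daily mean pressure without a baseline term, a pre-first-dose reading is implied for every woman, and nothing in the described randomisation balances it. For assumed correlations of 0.14 to 0.5, the variance forgone on a single post-dose value is about 2% to 25%. The low end applies if the entry threshold restricts the range strongly. An average over several days could gain more. The point reaches the daily systolic and diastolic means directly, and the primary outcome only if the same model is used for it.

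**What to change.** In the Data analysis plan, prespecify the last reading before the first dose as a covariate in the blood-pressure model, either ANCOVA or a mixed model for repeated measures. Match it to the outcome: systolic for daily mean systolic pressure, diastolic for daily mean diastolic pressure, and mean arterial for mean arterial pressure if this model is the primary analysis. State whether it is.

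The cost is one sentence and one degree of freedom per model. No new data are needed and the sample size stays as it is. Optionally, describe baseline characteristics by arm without p values; this improves reporting only.
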